### Missing data

2.11

There are repeated measurement data (including RF_CSA_) in our research, and some data may be missing during the experiment. RF_CSA_ is 1 of the primary outcome indicators; if the baseline RF_CSA_ (the first measured value) is missing, no interpolation will be performed. In other situations, we will deploy a diagnostic analysis related to missing data. The ratio of missing data will be summed in each group and at each time point, and the threshold of this ratio is set to 5%. If the missing data is above the threshold, the Little test will be conducted. Otherwise, a specified primary and/or secondary outcome has less than 5% of missing data, a complete case analysis without interpolating the missing values. We will then analyze the complete cases without data imputation if the complete case value is implied to be a random missing by Little test. When Little's test betokens that the complete case data set is not a random missing, the threshold estimates and their 95% CIs will be proclaimed after implementing a worst- and best-case scenario imputation for the missing values. Multiple imputations (MI) will not be performed if the worst- and best-case analyses concede for the same conclusion. Oppositely, statistical software will create ten MI data sets beneath the hypothesis of data missing at random. After MI, our research team will pool the results of the trial of the intervention effect and 95% CI of the analyses of each data set.

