#### Measurement of RF_CSA_

2.8.1

We will measure the RF_CSA_ on days 1, 3, 5, 7, 10, and 14 by B mode ultrasonography, using a 12L-SC (8.0-13.0 MHz, 7cm) linear array (Venue 50, GE Healthcare) at the First Affiliated Hospital of Guangzhou University of Chinese Medicine. RF_CSA_ will be measured on days 18, 21, 24, 28 if the patient continues to stay in the ICU. Patients will be prone to a 30° upwards incline at the head, except where the clinical conditions dictate otherwise. An excess of gel will be applied to minimize distortion. The transducer should be placed perpendicularly along the superior aspect of the upper leg, two-thirds of the distance between the anterior superior iliac crest and the superior patellar border. RF_CSA_ will be taken as an average of 3 consecutive measurements within 10% of 1 another. (A larger RF_CSA_ indicates a larger muscle mass). The point of measurement will be marked on the skin, and the same limb and location will be measured at each time point.^[1,24]^

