### Statistical analysis

2.10

All available data will be analyzed descriptively. For continuous data, the normality test will be applied at the very beginning of the analysis. We will bewrite the results as the means, standard deviations, and 95% confidence intervals (CIs) for continuous data that conform to the normal distribution; medians, quartiles, and ranges for rank data and continuous data that do not fit the normal distribution; and percentages for discrete data.

The change in the RF_CSA_ from baseline will be analyzed by a generalized additive mixed model of repeated measures design. Analysis of the time-to-event outcome (at day 28, day 90, six months, and 1 year after the admission of ICU) will be conducted by applying Kaplan-Meier curves. Kaplan-Meier survival curves will be performed to describe the survival rate between the 2 groups, and the log-rank method will be used to compare the survival rates of the acupuncture group and control group. Multivariate Cox proportional hazard regression models will be used to analyze several constituents (such as acute physiology and chronic health evaluation-II, SOFA score, demographic and diagnostic data), adjust for covariates, and correct for confounding. Our team will use similar approach mentioned above to analyze secondary outcome measures when they can be expressed as time-to-event outcome dimensions. All regression analyses (generalized additive mixed models, log-rank analysis, multivariate Cox proportional hazard regression models) will include the same covariates as the primary analysis. If there are any measurable differences between the 2 study groups with regard to prognostic factors, a propensity score analysis will be applied to assess the sensitivity of the results to any treatment allocation biases. The propensity score will be set for the main outcome. After the 2 sets of data are analyzed according to the previous analysis, the patients will be matched with the propensity score, and then the main outcomes of the matched 2 groups will be compared again to see if there are any similarities or differences between the 2 groups before and after the match. If they are the same, the results are stable; however, a difference means that there are factors affecting the evaluation of the outcome before the match, and these factors will need to be explained.

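### The 5% threshold and Little's test decide whether complete cases are analysed, but non-rejection at 49 per group does not show that data are missing completely at random, and the rule sits badly with the planned mixed model

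*Protocol article*

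**What the plan says.** Section 2.11 (Missing data) sets out a sequence of decisions. If the first RF_CSA value is missing, it is not filled in. Otherwise the extent of missingness is assessed first: "The ratio of missing data will be summed in each group and at each time point", against a limit of 5%. Below the limit the wording is: "a specified primary and/or secondary outcome has less than 5% of missing data, a complete case analysis without interpolating the missing values". Above it, Little's test is run, and the team will "analyze the complete cases without data imputation if the complete case value is implied to be a random missing by Little test". If the test points to non-random missingness, worst-case and best-case imputations follow. The last step is conditional on those two: "Multiple imputations (MI) will not be performed if the worst- and best-case analyses concede for the same conclusion". Ten imputed data sets under missing at random are created only if they disagree.

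Section 2.10 (Statistical analysis) states that the change in RF_CSA, a primary outcome, "will be analyzed by a generalized additive mixed model of repeated measures design". Section 2.8.1 schedules the scans "on days 1, 3, 5, 7, 10, and 14 by B mode ultrasonography", that is, baseline plus five later visits, and adds: "RF_CSA_ will be measured on days 18, 21, 24, 28 if the patient continues to stay in the ICU".

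**The concern.** Little's test has missing completely at random as its null hypothesis. Section 2.11 treats failure to reject as grounds for analysing complete cases. At 49 per group that is weak evidence, because the test can easily miss dependence on earlier values and cannot rule out dependence on the unseen values at any sample size. Allocation is by suitability for acupuncture and willingness (Section 2.7), so the reasons for missing a scan could well differ between the arms.

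The rule also appears to pull against Section 2.10. A likelihood-based mixed model uses every observed scan and is valid under missing at random without imputation. A complete-case restriction, read literally, discards the observed scans of any patient with one gap. At stake are the size and representativeness of the data behind a primary outcome, in a study meant to inform a multicentre one.

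**Working it through.** **1. The plan's own sample size (Section 2.3).** Inputs: 12.5% and 39.3%, alpha 0.05 (taken as two-sided, which the text does not state), power 0.80, ratio 1:1. With the unpooled normal approximation:

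n = (1.960 + 0.842)² × (0.125×0.875 + 0.393×0.607) / (0.393 − 0.125)² = 7.849 × 0.3479 / 0.0718 = 38.02, rounded up to 39 per group.

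39 / (1 − 0.20) = 48.75, so 49 per group and 98 in total. Both stated figures reproduce. The 20% allowance is implied, not stated.

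**2. What the 5% limit permits, in whole patients.** Per group and visit, 2/49 = 4.1% passes and 3/49 = 6.1% triggers Little's test. The post-baseline visits scheduled for everyone are days 3, 5, 7, 10 and 14. If complete case means listwise deletion:

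- different patients missing at each visit: 5 × 2 = 10 of 49 = 20.4% per group (20 of 98), leaving 39 per group;
- independent missingness: 1 − (47/49)^5 = 18.8%, about 18 of 98;
- the same patients missing throughout: 2 of 49 = 4.1%.

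The first line is the ceiling. It uses exactly the margin between 49 and 39, with no test run.

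**3. Power of Little's test, same mechanism in both arms.** Assumptions, none from the documents: 98 patients, 6 visits, AR(1) correlation 0.8, 15% missing at day 14 depending on the day-10 value, log-odds slope 0.5 or 0.8 per SD (odds ratio 1.65 or 2.2). Simulated rejection was 20% and 48%; a repeat with 3,000 runs gave 21% and 47%. Under missing completely at random it was 4.6%, so the test is correctly calibrated.

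**4. Mechanism differing by arm.** Assumptions: 49 per group, five post-baseline visits, percentage change with SD 4 to 10, correlation 0.85, dropout at days 10 and 14 with a baseline probability of 5-15% per visit, slopes 0.5 to 1.0, no true effect, 300 runs per setting.

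| Mechanism | Pooled rejection |
|---|---|
| Depends on previous value, one arm only | 6-29% |
| Depends on previous value, opposite directions by arm | 4-8% |
| Depends on the unseen value, differing by arm | 5-24% |
| Depends on previous value, slope 1.0, same direction in both arms | 66-92% |

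The test does well only in the last row, where bias in the treatment difference is near zero. In the first two rows the complete-case difference at day 14 was biased by about 0.3 to 4.8 percentage points, and essentially as much among the trials where the test did not reject. A likelihood analysis of all observed values was biased by 0.2 points or less. Settings with identical mechanisms in both arms gave chance values up to 0.28, so the 0.3 at the low end cannot be told from simulation noise. In the third row the all-records analysis was itself biased, by about 0.15 to 1.7 points, against 0.5 to 5.6 for complete cases.

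**The case against.** **Section 2.11 may mean only that nothing is imputed.** It describes complete-case analysis as leaving missing values unfilled, counts missingness by time point, and never says that a patient with one missed scan is removed. If the mixed model is then fitted to all visits, no scans are lost. This stands: a reader might infer that the protocol deletes partial series, but that is one reading of an ambiguous term. The use of Little's test is unaffected.

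**The loss is bounded.** A reader might compute 1 − 0.95^5 = 22.6%, or 22 of 98, and conclude that the loss exceeds the dropout allowance. Counted in whole patients it cannot: the ceiling is 20 of 98, equal to the allowance. Even that is unlikely. Sections 2.4.3 and 2.4.4 require survival through the ICU stay and exclude stays under 7 days, so death or discharge should not empty days 3, 5 and 7. Loss through discharge falls mainly on days 10 and 14, at most 4/49 = 8.2% per group below the limit.

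**Non-rejection is not harm.** A reader might take the 52-80% of trials without rejection in step 3 as the share with a biased treatment effect. They are not. With the same mechanism in both arms, bias in the between-group difference is about zero with no true effect and 0.01-0.02 SD with an assumed effect of 0.5 SD; the overall mean moves by 0.06-0.09 SD. Material bias needs a mechanism that differs by arm, which is plausible here but assumed.

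**The test is not powerless.** Saying that it cannot detect bias at this size would be too strong. It finds strong shared dependence, and run separately by arm it rejected in at least one arm in 9-78% of runs.

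**Days 18-28.** A reader might infer that a complete-case set would keep only the longest ICU stayers. Section 2.11 does not define complete cases over those scans, and a discharged patient has none scheduled.

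**Skipping multiple imputation when the extremes agree.** The conclusion is then robust, and no harm to it is shown. What is lost is an estimate under missing at random.

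**Conclusion.** The point holds in a limited form. Section 2.11 fixes a rule under which failure to reject Little's test licenses a complete-case analysis of a primary outcome. At 49 per group that inference is unsound: rejection is about 20-48% under the assumed moderate dependence, and 4-29% for a pooled test where dependence on earlier values differs by arm. These figures, and the 0.3 to 4.8 point bias, rest on assumed variances, correlations and mechanisms. They show what the rule can let through, not what will happen in this trial.

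The data loss of up to 10 of 49 per group is a ceiling and depends on reading complete case as listwise deletion. It needs no assumption about mechanism, but it does need different patients to be missing at every visit. Sections 2.10 and 2.11 must be reconciled in either case, because the text does not say whether partial RF_CSA series enter the mixed model. This should be changed before analysis.

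**What to change.** In Section 2.11, remove the 5% limit and Little's test as conditions for choosing the analysis; missingness by group and visit can still be reported. State in Section 2.10 that the primary RF_CSA analysis is the mixed model fitted to all observed scans at the visits scheduled for everyone (days 1 to 14), under missing at random, with partial series kept. Report the scans on days 18 to 28 descriptively, since they exist only for patients still in the ICU.

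Keep the worst-case and best-case analyses and add delta-adjusted imputation, both as sensitivity analyses that do not decide whether the missing-at-random result is reported. The delta adjustment is needed because the mixed model does not remove bias when missingness depends on unseen values.

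The cost is revised wording and a little more analysis work. No new data are required.

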### Data monitoring

2.12

All data will be kept confidentially. Participants will be consigned with a code that will be adopted for all data management and analyses. The paper version of CRFs will be stored in a locked file cabinet. Coded electronic data will be stockpiled on a computer server at the First Affiliated Hospital of Guangzhou University of Chinese Medicine for the duration of the study. Entree to the computer records will be password-protected, and data will be accessible only to the investigation team. A data monitoring committee has been set up to conduct quality control assessments on the data. The completeness, consistency and plausibility of data will be supervised regularly and systematically and will be reported to the administration committee. The primary investigator (PI) will have access to the final deidentified data set. The reporting of adverse events, serious adverse events (SAEs) and suspected unexpected serious adverse reactions will appraise the safety of the study intervention. A descriptive analysis will be forwarded to the data monitoring committee regularly to assess the safety of the study intervention.

### Adverse events

2.13

In this study, adverse events will be defined as follow:

(1)Fainting: Fainting means that the patient suddenly developed dizziness, palpitation, nausea, and even syncope during the acupuncture process; fainting is common in the acupuncture process.(2)Broken needle: when the acupuncture needle breaks inside the patient.(3)Hematoma: swelling and pain caused by a subcutaneous hemorrhage at the acupuncture site during or after the needle puncture.(4)Bent needle: When the needle is inserted into the acupoint, the needle is bent in the body.(5)Sticking of the needle: After the needle is inserted, when lifting and twisting the needle or when the needle is pulled out, the needle feels very heavy, tight, and even twitching; the needle is difficult to twist or remove, and the patient feels pain abnormal.(6)Infection: infection at the acupuncture site after acupuncture.

If the above situations occur, they will be urgently handled by the acupuncturist and the ICU physician; if the researcher determines that the research plan does not needed to be adjusted, the research will continue. If the condition changes and the study treatment plan need to be stopped or changed, the subject will be withdrawn from the study and the events will be recorded in detail. All subsequent clinical treatments are based on the principle of saving the life of the subject and improving the prognosis of the disease. For all adverse events, the adverse event report form needs to be completed and the events need to be reported.

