#### Acupuncture treatment

2.5.1

According to the patient's (and/or their relatives’) willingness and the clinical routine, a group of physicians will assess the acupuncture treatment within 24 hours in patients who meets the inclusion criteria 1 to 5. All physicians are required to have at least 3 years (or 300 hours) of practical experience with acupuncture. The acupuncture treatment will be performed by stainless steel needles (0.30 mm × 40 mm; 0.30 mm × 25 mm; Suzhou Medical Supplies Factory Co., Ltd., Suzhou City, China). The acupuncture treatment will be performed by the technique of lifting, thrusting, twirling and rotating the needle until the patient is being “De-qi” (getting a numbness or other acupuncture feeling). Two points that do not cross the joint will be chosen for electrical stimulation. The needle will be kept in place for approximately 30 minutes. By the time we remove the needles, a clean cotton balls will be pressed to the skin to prevent bleeding.

All patients must be treated at “3 obligatory basic acupuncture points”: ST36, ST40 and LI10. Furthermore, at least 3 additional acupuncture points will be selected according to the principles of traditional Chinese medicine (for example, if the patient has a mental disorder manifestation, acupoints such as GV20, GV24, and EX-HN3 can be added to promote the patient's waking). Additional acupoints could be applied, and ear acupuncture points might also be included. All acupoints selected in each session will be recorded. A traditional Chinese syndrome diagnosis is required, and the diagnosis will be documented. Acupuncture treatment will be performed twice a day and lasts for 30 minutes. If the included subjects do not meet the exclusion criteria and do not terminate their participation in study, they will receive acupuncture treatment during their entire ICU stay. If the patient is discharged from the ICU, the acupuncturist will continue to follow the patient until the 14-day acupuncture session is completed. Both the acupuncture group and the control group will receive basic sepsis treatment. The selection of acupuncture points is listed in Table 1.

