#### Patient follow-up

2.8.7

After the subject is discharged from the ICU, the researcher will not perform any form of intervention. According to the requirements of the observation indicators and their time points, follow-up data collection and filling will be performed 28 days, 90 days, 6 months and 1 year after ICU admission; patients will be followed until the follow-up time expires or the subject dies. The follow-up data collection includes the incidence of time-to-event, the FIM^TM^ scale and so on. Follow-up will be conducted by clinic follow-up and telephone follow-up. The investigator will notify the patient to return to the clinic for follow-up at a fixed time point. If it is inconvenient for the patient to go to the clinic, the follow-up will be conducted over the phone. If the patient refuses to proceed and asks to quit at any time during the follow-up, is the patient will be withdrawn from the study. If the patient cannot be contacted more than 3 times during the follow-up period, by any contact method (including telephone, mail, and various social software), is the patient will be considered lost to follow-up.

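### The adverse-event rule withdraws patients from the study, not only from needling, when treatment must be stopped or changed, so avoidable loss of outcome data falls almost entirely on the acupuncture arm

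*Protocol article*

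**What the plan says.** Section 2.13 (Adverse events) defines six events: fainting during acupuncture, a broken needle, hematoma at the needle site, a bent needle, a stuck needle, and infection at the needle site. It then gives a sequence:

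- First, "If the above situations occur, they will be urgently handled by the acupuncturist and the ICU physician".
- If the researcher judges that no adjustment of the plan is needed, the research goes on.
- If not, "If the condition changes and the study treatment plan need to be stopped or changed, the subject will be withdrawn from the study". Details of what happened are then documented.

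Section 2.8.7 (Patient follow-up) sets the general rule that "patients will be followed until the follow-up time expires or the subject dies". It names two early exits. One is loss of contact after repeated attempts. The other is the patient's own decision: someone who "refuses to proceed and asks to quit at any time during the follow-up, is the patient will be withdrawn from the study".

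Section 2.11 (Missing data) has the proportion of missing values "summed in each group and at each time point, and the threshold of this ratio is set to 5" percent. Below that, complete cases are analysed. Above it, Little's test is run, and complete cases are still used if the test indicates random missingness. Otherwise worst-case and best-case imputation follows, and multiple imputation if those two disagree.

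**The concern.** Stopping a treatment and leaving a study are different events. A patient who has a needle-site infection and can no longer be needled still has a thigh muscle to scan, strength to test, and a survival and readmission status to record. Section 2.13 joins the two events, and it does so by the investigators' decision and not the patient's.

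The triggers exist in one arm only. Groups are formed by suitability and willingness, not by randomisation (section 2.7), so the comparison already depends on adjustment for selection. A rule that removes patients from one arm after treatment has begun adds a second selection that baseline covariates or a propensity score need not capture.

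The exposed outcomes are all three primary outcomes (change in rectus femoris area, MRC sum-score, and time to death or unplanned return to ICU for invasive ventilation), plus FIM up to 1 year. In the Kaplan-Meier and Cox analyses these patients would be censored at withdrawal. Because the clause requires that the patient's condition has changed, that censoring may be related to prognosis.

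**Working it through.** **1. Who can trigger the rule.** Each of the six listed events requires a needle. Control patients receive basic treatment and exercises (section 2.7), so they cannot have one. Read alone, the withdrawal sentence could reach a control patient whose care is changed, hence almost only and not only.

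**2. What withdrawal means.** Sections 2.13 and 2.8.7 use the same phrase for leaving the study. In 2.8.7 it describes a patient who quits follow-up. The natural reading is that it has the same effect in 2.13, where the patient has not asked to quit. Nothing in 2.8.7, 2.11 or 2.13 says that such patients are still assessed.

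**3. Which data are exposed.** Needling runs through the ICU stay and, after discharge, "until the 14-day acupuncture session is completed". MRC sum-score is taken at first awakening and at ICU discharge, and FIM at day 28, day 90, six months and 1 year. A withdrawal during the course can therefore cost later scans, the discharge MRC sum-score, the FIM series and most of the time-to-event follow-up.

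**4. The planned sample size (section 2.3).** With rates 0.125 and 0.393, two-sided alpha 0.05, power 0.80 and unpooled variance:

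n = (1.960 + 0.842)² × (0.125 × 0.875 + 0.393 × 0.607) / (0.393 − 0.125)² = 7.85 × 0.348 / 0.0718 = 38.0, rounded up to 39 per arm.

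39 / (1 − 0.20) = 48.75, which rounds up to 49. Both stated figures reproduce, with an assumed dropout of 20% (the rate is not stated).

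**5. The 5% threshold.** 0.05 × 49 = 2.45 patients. Then 2/49 = 4.1% (below) and 3/49 = 6.1% (above). Up to two such withdrawals, with no other loss, lead straight to complete cases. Three take the acupuncture arm over the line while the control arm can stay at 0%, and complete cases can still follow after Little's test. This assumes that withdrawn patients stay in the denominator of 49.

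**6. What selective loss could do (assumed inputs).** Suppose acupuncture has no effect and the true risk is 39.3% in both arms. This is the control rate in section 2.3, borrowed from a polyneuromyopathy outcome. Let a fraction w of the acupuncture arm be removed, with risk p. The retained risk is (0.393 − w × p) / (1 − w).

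| Removed, w | p = 20% | p = 39.3% | p = 60% | p = 80% |
|---|---|---|---|---|
| 5% | 40.3% | 39.3% | 38.2% | 37.2% |
| 10% | 41.4% | 39.3% | 37.0% | 34.8% |
| 20% | 44.1% | 39.3% | 34.1% | 29.1% |

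For example, w = 10% and p = 20% gives (0.393 − 0.020) / 0.90 = 41.4%. The error can favour either arm, and it is zero if those removed have the arm's average risk. Neither w nor p is given in the documents.

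**7. Power.** At 12.5% against 39.3% with 49 controls (pooled-variance formula), power is 0.869 with 49 acupuncture patients, 0.848 with 44 and 0.821 with 39. The issue is selective loss, not power.

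**The case against.** The best defence is that the clause is narrow. A needle event alone withdraws nobody: the researcher must judge that adjustment is needed, the patient's condition must have changed, and the plan must have to be stopped or changed. Section 2.13 calls fainting common, but a faint that is handled and needs no adjustment leaves the patient in the study. Section 2.5.1 already individualises the additional points, so varying those is arguably within the plan. All of this stands and limits how often the rule would act. It does not alter what happens when it does act.

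Second, the analysis has some protection. Data before withdrawal are not said to be discarded, mixed models and survival methods use partial follow-up, the sample size allows for dropouts, and the check by group and time point could expose one-sided loss. This also stands in part. None of it recovers the missing outcomes, and a result from Little's test that does not reject randomness is weak reassurance when few patients are missing.

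Third, a condensed article may leave data collection after withdrawal to the full protocol or analysis plan. Silence on that would be no finding. The point here is a stated rule that ends participation.

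A reader might also infer a safety gap. Section 2.5.1 says that subjects who "do not meet the exclusion criteria and do not terminate their participation in study, they will receive acupuncture treatment during their entire ICU stay", and the exclusion criteria do not name the edema, coagulopathy or local infection that section 2.7 treats as unsuitable. The documents do not support that inference. Section 2.7 can be read to cover later sessions, section 2.13 already allows treatment to be stopped, and Tables 2 and 3, which include the bedside protocol, are not visible.

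**Conclusion.** The concern holds as a fault in a stated rule. Section 2.13 turns a necessary stop or change of needling into an exit from the study that the patient did not request. It does so almost only in the acupuncture arm, and section 2.11 does not reliably repair the resulting loss.

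No size of bias can be given. A reader might infer that the rule makes acupuncture look better by removing sicker patients. The documents do not show this: the listed triggers are procedural, inclusion criterion 6 already limits the cohort to ICU survivors, and no frequency or prognosis is stated for those withdrawn. Nor should the number of needling sessions be taken as a measure of the problem, because it counts exposure and not withdrawals.

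The conclusion rests on reading withdrawal in 2.13 as it is used in 2.8.7. The threshold figures (4.1% and 6.1%) also assume that withdrawn patients remain in the denominator of 49. That is not certain, because needling starts on inclusion criteria 1 to 5, before criterion 6 is known. If they were left out of the 49, the loss would not appear in the missing-data check at all.

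**What to change.** Reword section 2.13 along these lines: when an adverse event requires needling to be stopped or changed, only the treatment is stopped or modified. The patient remains in the acupuncture group, in all scheduled assessments and 1-year follow-up, and in the analysis. Follow-up ends early only if consent is withdrawn or the loss-to-contact rule in section 2.8.7 applies.

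The cost is small. Section 2.8.7 already provides clinic visits with telephone as the fallback, and section 2.13 already requires the event to be recorded. The one downside is that the acupuncture group will include some patients with an incomplete course, which may dilute the contrast slightly. That fits a trial described as pragmatic.
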